### Secondary and supplementary analyses

From the primary analysis model, the effect during hospitalization and the post-intervention effect (change from 4 weeks to 6 months post discharge) will be estimated. For the secondary outcomes, similar analyses will be performed. Moreover, all analyses will be using adjustments for baseline DEMMI. To account for imbalances in in-hospital time, a sub-analysis will be performed for the effect during hospitalization and the effect from baseline to end of intervention adjusted for length of stay. Additionally, the unadjusted repeated model will be carried out following the per protocol principle, comparing patients who have fulfilled the compliance criteria with the control group. All between-group differences will be expressed as the average difference in change from baseline. The analyses outlined above will all be reported in the main trial manuscript regarding effect of the strength training program.

If additional funding is obtained, more patients will be included to increase the sample size to obtain sufficient power to model statistical interactions and perform secondary analyses (described below), which will be published subsequently. To investigate the possible influence of confounders and modifiers on the effect of the intervention on DEMMI, an unadjusted analysis of variance of the between-group change from baseline to 4 weeks post discharge in the DEMMI score will be performed. In addition, this model will be extended by adjusting for all and each of the potential confounders and modifiers one by one. Confounding effects will be evaluated by comparing the unadjusted effect of group with the adjusted effects. Moreover, to investigate whether or not the effect of the intervention is modified by the potential confounders and modifiers the adjusted models will be extended with an interaction term between group and the potential confounders and modifiers. Similar analysis will be performed with 24-h mobility (average time spent standing or walking per 24 h) and with those of the secondary outcomes that showed a significant between-group difference in the primary analysis. Also, a logistic regression with compliance as the outcome and each of the potential confounders and modifiers as covariates will be performed. All analyses will follow both the intention-to-treat and the per protocol principle.

To investigate the effect of the intervention on cognition (MCI status, MMSE, OMC, HVLT, DSST, Trails A and B) at 4 weeks, the following analyses will be performed. A generalized logistic regression for MCI status and an analysis of variance for MMSE, OMC, HVLT, DSST, and Trails A and B will be used with group as the independent variable. The analyses will follow the intention-to-treat principle with multiple imputation for missing values. Moreover, these analyses will also be performed adjusting for baseline OMC, baseline DEMMI, gender and age, depression, health status, nutritional state, self-reported physical activity, pain, medications, length of stay and 24-h mobility using assessments from the first week after discharge, and possible interactions with group will be analyzed. Additionally, the models will be repeated following the per protocol principle comparing patients. All results will be expressed as estimated means’ differences between the intervention and control group with the corresponding 95 % confidence intervals.

All models will be investigated for goodness-of-fit (linearity, variance homogeneity and normal distribution of residuals) by visual inspection of plots and remodeling will be performed accordingly. All statistical tests will be performed using SAS (SAS Institute Inc., Cary, NC, USA) and *p* values ≤0.05 will be considered statistically significant. However, for all analyses evaluating potential modifiers and confounders of the intervention *p* values ≤0.01 will be used to account for multiple testing. No interim analysis will be made.

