After inclusion, baseline assessments will be performed whereafter the patients will be randomized to either: (1) intervention: progressive strength training during hospitalization and the first month after discharge (home-based), or (2) control: usual care. Shortly after discharge, four weeks (primary end point) and 6 months (follow-up) after discharge the patients will be assessed in their own homes. Figure 1 shows the study flow.

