### Intervention group

Patients in the intervention group will receive 1:1 supervised progressive strength training daily on weekdays during hospitalization and three times per week for 4 weeks (12 training sessions, 1:1 supervised) after discharge. To account for possible cancellations, i.e. due to illness or other obstacles for training completion, distributing the 12 in-home training sessions over a maximum of 5 weeks will be allowed. The training will take place in the patient’s bedroom during hospitalization and in the patient’s own home after discharge.

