
### Additional variables

Descriptive variables and possible confounders and modifiers for exploratory analyses will be collected. Descriptive variables will include: education, living status, history of smoking, use of ambulatory devices, use of municipal help, history of falls during the last year, Nutritional Risk Screening (NRS) [88–90], the New Mobility Score (NMS) (recall of mobility 2 weeks before admission and on the day of admission) [91, 92] and the Cumulated Ambulation Score (CAS) [93]. Possible confounders and modifiers will be assessed: gender; age; cognition by the Short Orientation-Memory-Concentration test (OMC) [94], the Mini Mental State Examination (MMSE) [95], the Trail Making Test (Trails) [96, 97], the Digit Symbol Substitution Test (DSST) [98], and the Hopkins Verbal Learning Test – Revised (HVL-R) [99, 100]; depression by the Geriatric Depression Scale (GDS) [101]; health status by the EuroQol instrument (EQ-5D) [102]; nutritional state by the Mini Nutritional Assessment (MNA) [103]; self-reported physical activity by a four-level questionnaire [104, 105]; pain before and after training by the Verbal Ranking Scale (VRS) [106, 107]; medications, history of training before admission, and history of training in the municipality after discharge. Moreover, baseline level of DEMMI and 24-h mobility using assessments from the first week after discharge will be treated as possible confounders and modifiers. Based on the cognitive assessments, patients will be categorized as having mild cognitive impairment (MCI) or not, and those with MCI will be further sub-categorized as amnestic-MCI, non-amnestic MCI or multiple-MCI [108]. These categories will be used in the analyses.

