### Data collection

The primary investigator and a team of three assistant investigators will perform all baseline and follow-up assessments. All four investigators are trained physiotherapists with 1 to 15 years of experience.

The admission assessments will be performed on the acute medical admissions ward or on an internal medicine ward at Copenhagen University Hospital, Hvidovre, Denmark, within the first 48 h after admission. All follow-up assessments will be performed in the patient’s own home, and the same investigator will assess the same patient at all assessments whenever logistically possible, to promote patient retention.

During each training session the supervising physiotherapist will complete an exercise diary consisting of information about the level of exercise attained according to the progression models, the extra load added (kg), and the number of sets and repetitions performed at each level. Self-reported pain will be registered immediately before and after each training session by the use of the VRS. Moreover, the physiotherapist will register reasons for non-participation as well as the amount of protein consumed after each training session. The patient time line including data collection is presented in Table 3.

**Table 3 Tab3:** Patient timeline

	Study period						
Time point	Admission	Baseline	Hospital intervention	Discharge assessment	Home intervention	4-week assessment	6-month assessment
		≤48 h after admission	Daily during hospitalization	In patient’s home	3 times per week for 4 weeks in patient’s home	In patient’s home	In patient’s home
Enrollment							
Eligibility screen	X						
Informed consent	X						
Study groups							
Strength training		X	X	X	X	X	X
Control		X		X		X	X
Assessments							
Baseline assessment^a^		X					
Primary outcomes		X		X		X	X
Secondary outcomes		X		X		X	X
Descriptive variables and possible confounders and modifiers		X		X		X	X

^a^See Table 2 for a detailed description of assessed variables

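### Several supplementary analyses condition on variables that arise after randomization (compliance in one arm, length of stay, first-week activity, discharge cognition), so randomization does not protect them and they are at risk of bias

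*Protocol article*

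**What the plan says.** **Sequence.** Under Study sample and recruitment procedure: "After inclusion, baseline assessments will be performed whereafter the patients will be randomized to either" of the two groups. Data collection places the baseline assessment "within the first 48 h after admission". Under Intervention group, patients then receive "supervised progressive strength training daily on weekdays during hospitalization and three times per week for 4 weeks" after discharge.

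**Analyses for the main trial paper** (Secondary and supplementary analyses):
- Length of stay. The reason given is "To account for imbalances in in-hospital time", and the plan is that "a sub-analysis will be performed for the effect during hospitalization and the effect from baseline to end of intervention adjusted for length of stay".
- Per protocol. The unadjusted repeated model is rerun, "comparing patients who have fulfilled the compliance criteria with the control group". The Compliance section sets the criterion at 80% of sessions with at least two sets each.

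**Analyses for later publication**, with a sample-size extension that depends on further funding:
- Under Additional variables, baseline DEMMI and "24-h mobility using assessments from the first week after discharge will be treated as possible confounders and modifiers". MCI category, derived from the cognitive tests, is also to be used in the analyses.
- The cognition models adjust for a list that includes depression and ends with "length of stay and 24-h mobility using assessments from the first week after discharge, and possible interactions with group will be analyzed".
- Confounding is judged by comparing the unadjusted group effect with the adjusted ones.

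Table 2 records MMSE, Trails, DSST, HVLT and GDS from discharge onward only. OMC is the only cognitive test with a baseline value. Post-discharge 24-h mobility is itself the first secondary outcome.

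**The concern.** In a randomized comparison, a variable can confound the group effect only through chance imbalance in something already settled at allocation. Length of stay, first-week activity and discharge-measured cognition are settled later, after in-hospital training has begun, and first-week activity is recorded when home training is also starting. If training changes them, adjustment removes part of the effect being estimated. If unmeasured illness severity drives both the covariate and DEMMI, adjustment can also open a non-causal path.

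The rule for detecting confounding makes this worse. When the group effect shrinks after adjusting for activity, the plan would call it confounding, although mediation would produce the same pattern.

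The per-protocol contrast has a different fault. Only the intervention arm can meet the compliance criterion. That arm therefore loses the patients who could not keep up training, while the control arm keeps their counterparts. The protocol itself expects sessions to be cancelled because of illness (Intervention group) and notes compliance problems in earlier hospital-to-home programs (Background). A prognostic difference between compliers and non-compliers is therefore plausible.

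At stake is how two secondary results printed beside the primary one will be read, and how the later modifier papers will be interpreted.

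**Working it through.** **Plan's own figure.** Inputs from Sample size: difference 10, SD of change 12.8, two-sided 5%, power 80%. The two-sample *t* test solution is 26.7, so 27 per arm, with power 80.4%. The stated figure is reproduced and is not in dispute. It supplies the SD and n used below.

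**Per-protocol contrast with no true effect, simple mixture.** Let p be the share who comply and g the DEMMI points by which non-compliers would do worse. Randomization gives both arms the same mixture.
- Complier mean = c. Control mean = c − (1 − p)g.
- Spurious difference = (1 − p)g.
- p = 0.8, g = 5: 0.2 × 5 = 1.0. p = 0.6, g = 10: 0.4 × 10 = 4.0.

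Neither p nor g is in the document. Both ranges are assumptions.

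**Same contrast, second model.** Compliance depends on a latent normal variable that correlates r with DEMMI change (r assumed). Spurious difference = r × 12.8 × φ(z)/p, where φ is the standard normal density and z its (1 − p) quantile.

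| Compliant | r = 0.2 | r = 0.3 | r = 0.5 |
|---|---|---|---|
| 80% | 0.9 | 1.3 | 2.2 |
| 60% | 1.7 | 2.5 | 4.1 |

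Simulated two-sided type I error, starting from 27 per arm and dropping non-compliers from one arm:
- 80% compliant: 6.4% (r = 0.3) and 9.2% (r = 0.5).
- 60% compliant: 8.9% (r = 0.3) and 17.1% (r = 0.5).
- r = 0: about 5%, as it should be.

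**Scale.** The standard error at 27 per arm is 12.8 × √(2/27) = 3.5 points. With 60% compliant (about 16 patients) it is 12.8 × √(1/16 + 1/27) = 4.0. A spurious 4 points is therefore about one standard error.

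**Adjusting for a post-randomization covariate.** Suppose a true effect of 10. Training shifts the covariate by a SD units in the favourable direction, and the covariate correlates r with outcome within arm (a and r assumed). Adjusted effect = 10 − r × 12.8 × a.
- a = 0.25, r = 0.2: 10 − 0.64 = 9.4.
- a = 0.5, r = 0.5: 10 − 3.2 = 6.8.
- a = 0: 10, unchanged, provided no other path is open.

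**The case against.** The primary analysis is fixed as intention to treat and unadjusted, and nothing lets these analyses replace it. The confounder and modifier variables are collected for exploratory use, are tested at p ≤ 0.01, and belong to later papers. All of that stands and limits the scope of the point.

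A reader might infer that the adjusted estimates are biased as a matter of fact. The document does not support that. It nowhere says that training changes length of stay or first-week activity, and the in-hospital dose is roughly 10–15 minutes on weekdays. With no shift and no other open path, the adjusted effect is the same. Size and direction cannot be derived from the text.

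A reader might also infer that the per-protocol analysis would show a clear benefit from useless training, or that adjustment would hide a real one. The illustrations do not go that far. They give a spurious difference of at most about one standard error, and attenuation from 10 to between 9.4 and 6.8.

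The length-of-stay model has a legitimate motive. The interval from baseline to 4 weeks after discharge varies with the stay, and baseline predictors do not describe that. This supports keeping the model as description. It does not make the model a corrected treatment effect, because an imbalance in stay may be chance or may be a result of allocation.

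Finally, a complier-average effect with randomization as the instrument is not a clean replacement. It assumes no benefit below the 80% cut-off. Suppose compliers gain 10 and the rest gain 5 (assumed):
- 60% compliant: the intention-to-treat effect is 0.6 × 10 + 0.4 × 5 = 8, and 8/0.6 = 13.3.
- 80% compliant: it is 0.8 × 10 + 0.2 × 5 = 9, and 9/0.8 = 11.25.

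Both overstate the true 10. This objection stands and shapes the fix.

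**Conclusion.** The concern holds as a risk of bias in supplementary analyses. The conditioning variables arise after randomization, the plan specifies their use outright, and the article does not describe the resulting contrasts as non-randomized.

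- **Per protocol (main paper)** is the strongest element, because selection acts in one arm only and the model is unadjusted. A spurious benefit of 1 to 4 DEMMI points, 10–40% of the 10-point target, follows from assumed compliance of 60–80% and an assumed prognostic gap of 5–10 points.
- **Length of stay (main paper)** may remove part of the effect, but only if training changes the stay or adjustment opens another path.
- **First-week activity, MCI category and GDS (later papers, partly dependent on funding)** are wrongly classed as potential confounders of a randomized effect, and the comparison rule would misread mediation as confounding.

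The primary result is untouched, and the planned adjustment for baseline DEMMI is sound.

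**What to change.** 1. Restrict the confounder, modifier and covariate lists to values measured before randomization, for example baseline DEMMI, baseline OMC, age and gender. Drop first-week 24-h mobility and the cognition and depression measures first taken at discharge. Use baseline OMC for cognition.
2. Keep the length-of-stay model if wanted, but present it as descriptive and not as a corrected treatment effect.
3. Adjust the per-protocol contrast for baseline prognostic variables, label it a non-randomized comparison, and draw no efficacy conclusion from it. Adjustment reduces the selection only as far as the baseline variables capture it.
4. If a complier-average effect is added, use the number or proportion of sessions completed as the exposure. Otherwise, state that the binary 80% cut-off assumes no benefit below it and overstates the complier effect if partial training helps.

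Cost: changes of wording, plus one standard procedure if step 4 is taken. The intervals become wider, and the per-protocol figure will probably look less favourable. No change to data collection or sample size is needed.

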## Methods

### Study design

The study, which is called the Cross-Continuum Progressive Strength Training in Older Medical Patients – Copenhagen (STAND-Cph) trial, is a randomized, controlled, parallel-group (two groups), investigator-blinded, superiority trial being conducted in the Copenhagen area, Denmark. The trial investigates the effect of a simple, low-technology, supervised strength training program commenced during hospitalization and continued for 4 weeks after discharge (ClinicalTrials.gov-identifier: NCT01964482). The study is conducted as a full-scale trial following a feasibility study in which we found a progression model for loaded sit-to-stands feasible when used as a simple strength training exercise in older medical patients [61]. Participants will be randomized to either progressive strength training or usual care, and the primary end point will be 4 weeks after discharge (end of exercise period). In addition, the participants will be followed up after 6 months. Table 1 provides an overview of the trial characteristics.

**Table 1 Tab1:** Trial registration data

Data category	Information
Primary registry and trial identification number	ClinicalTrials.gov: NCT01964482
Data of registration in primary registry	14 October 2013
Secondary identifying numbers	The Ethics Committee of the Capital Region of Denmark: H-2-2012-115
	The Danish Data Protection Agency: 2007-58-0015
Source(s) of monetary or material support	Danish Regions/The Danish Health Confederation, The Lundbeck Foundation (UCSF) (grant numbers FP 07/2012, FP 48/2012 and FP 61/2013), the Research Foundation of Hvidovre Hospital, the Capital Region of Copenhagen, and The Danish Foundation for Research in Physiotherapy
Primary sponsor	Danish Regions/The Danish Health Confederation
Secondary sponsor(s)	The Lundbeck Foundation (UCSF), the Research Foundation of Hvidovre Hospital, the Capital Region of Copenhagen, and The Danish Foundation for Research in Physiotherapy
Contact for public queries	[name], TB ([contact])
Contact for scientific queries	[name], TB. Clinical Research Centre, Hvidovre Hospital, University of Copenhagen, Denmark
Public title	In-hospital and post-discharge training of older medical patients
Scientific title	Supervised progressive cross-continuum strength training compared with usual care in older medical patients: study protocol for a randomized controlled trial (the STAND-Cph trial)
Country of recruitment	Denmark

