### Randomization

Patients who consent to participate will be randomly allocated to either of the two groups. Randomization will follow a computer-generated block randomization list produced by the study coordinator (JP). Randomization is stratified within the two participating municipalities. The recruitment will follow a 2:1 allocation in one of the municipalities (A) and a 1:2 allocation in the other municipality (B). This randomization procedure is followed to comply with the capacity of the municipalities (the number of physiotherapists available).

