### Sample size

Based on data from an unpublished cohort study performed at Hvidovre Hospital, 25 consecutively included older medical patients had a mean change in the de Morton Mobility Index (DEMMI) [62] score of 1.8 and a standard deviation of 12.8 from admission to 1 month after discharge. A change of 10 points in the DEMMI score is considered a minimal clinically important difference in acute older medical patients [62]. To be able to detect a 10-point difference in the between-group change in the DEMMI score at the 4-week assessment (primary end point), we will need a sample size of 27 patients per study arm to obtain a type I error rate of 5 % and a power of 80 % for a two-sample *t* test of a normal mean difference with a two-sided significance level. We will continue to recruit patients until 54 patients have been assessed for the primary end point (4 weeks). In case of a skewed distribution of patients in the two groups (intervention and control), we will recruit until both groups contain 25 patients. We expect a maximum of 80 patients to be included in the study.

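### Comparing unadjusted with one-by-one adjusted group effects cannot identify confounders in the exploratory intention-to-treat analysis, and the screen omits municipality, the one confounder the design creates

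*Protocol article*

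**What the plan says.** All references are to the protocol article.

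- **Design.** Study design states that the trial "is a randomized, controlled, parallel-group (two groups), investigator-blinded, superiority trial". Randomization stratifies by municipality, with a 2:1 ratio in one and 1:2 in the other. Changes to initial plan adds a third municipality at 2:2.
- **The analysis.** Secondary and supplementary analyses starts from an unadjusted analysis of variance of 4-week DEMMI change. Then "this model will be extended by adjusting for all and each of the potential confounders and modifiers one by one", and "Confounding effects will be evaluated by comparing the unadjusted effect of group with the adjusted effects". The same section asks for both intention-to-treat and per-protocol versions.
- **Significance level.** A 0.01 level is set "for all analyses evaluating potential modifiers and confounders of the intervention", to allow for multiple testing.
- **Candidates.** Table 2 lists 16 possible confounders and modifiers. Additional variables adds baseline DEMMI and 24-h mobility from the first week after discharge, and describes the purpose as exploratory.
- **Status.** The work is done only if more funding allows a larger sample, and it is published after the main report. The size of that larger sample is not given.
- **Primary analysis.** This is a separate intention-to-treat mixed model, unadjusted for covariates, with municipality as a random variable.

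**The concern.** The method is the change-in-estimate approach of observational research, applied to a randomized factor. In observational data a shift after adjustment may reveal a common cause of exposure and outcome. Here exposure is assigned by a list, so within a municipality no patient characteristic influences it. What the comparison ranks is the size of accidental imbalance multiplied by prognostic strength.

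The later paper could therefore name as confounders covariates that merely happened to be unbalanced. It would also carry about 20 intention-to-treat estimates of one effect (1 unadjusted, 18 singly adjusted, 1 fully adjusted), with no statement of how the adjusted ones are to be read. Meanwhile the variable that the allocation scheme does tie to treatment group is not examined.

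**Working it through.** **1. The article's own figure.** Inputs from Sample size: "To be able to detect a 10-point difference in the between-group change in the DEMMI score" (10 points); "a standard deviation of 12.8 from admission to 1 month after discharge" (12.8 points); two-sided 5%; power 80%. The normal approximation gives n = 2 × (1.960 + 0.842)² × 12.8² / 10² = 25.7, so 26 per arm. The exact t test has power 0.789 at 26 and 0.804 at 27 per arm. The stated 27 per arm is reproduced, and 10 and 12.8 serve as inputs below.

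**2. Which candidates are baseline variables.**
- Measured at baseline (11): age, gender, OMC, two EQ-5D items, MNA, self-reported activity, pain (VRS), medications, earlier training, baseline DEMMI. Some are also measured later; I assume the baseline value is used.
- Only after randomization (7): MMSE, Trails, DSST, HVLT, GDS, training in the municipality after discharge, first-week 24-h mobility. In-hospital training has begun by then, so these may lie on the path from treatment to outcome.

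**3. What a shift is.** For one covariate, shift in group effect = estimated slope × difference in covariate means between arms (up to sign). Within a municipality the expected mean difference is zero. With correlation r between covariate and outcome, and the slope at its true value, the SD of the shift is 12.8 × r × √(2/n per arm).
- 27 per arm: 12.8 × 0.1 × √(2/27) = 0.35 points; at r = 0.2, 0.70 points.
- 80 per arm: 12.8 × 0.1 × √(2/80) = 0.20 points; at r = 0.2, 0.40 points.

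The slope is itself estimated, with a standard error of about 12.8/√54 = 1.74 per SD of the covariate at 54 patients. That exceeds the true slope of 1.28 at r = 0.1, so weak covariates also produce shifts, and simulation is needed.

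**4. How often the largest of 11 shifts exceeds 1 point.** Assumptions: true effect 10, SD 12.8, equal arms, independent covariates, r = 0.1 to 0.2, no true confounding. The 1-point cut-off is mine.

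| Total patients | At least one shift above 1 point |
|---|---|
| 54 | 66–88% |
| 80 | 38–74% |
| 160 | 5–32% |

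The article gives no enlarged sample size; 160 is illustrative. There the largest shift averages 0.6 to 0.9 points.

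**5. Dependence on the cut-off.** In a second simulation at 27 per arm, with 18 covariates treated as baseline and correlations of 0 to 0.3, at least one shift exceeded 2 points in 10–72% of trials and 5 points in at most 1.5%.

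**6. The 0.01 level.** The article defines no test of the difference between two adjusted estimates, so this level cannot be applied to a shift. If it were used to test baseline imbalance instead, 11 independent tests would give at least one false signal with probability 1 − 0.99¹¹ = 10%.

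**7. Municipality.** Suppose A and B contribute equally. A then supplies 2/3 of one arm and 1/3 of the other. An analysis ignoring municipality is biased by (2/3 − 1/3) × d = d/3, where d is the difference in mean DEMMI change between A and B: 1 point for d = 3, 2 points for d = 6. If the third municipality supplies a share h of patients at equal allocation, this becomes (1 − h) × d/3. Unlike the shifts in step 3, it does not shrink as the sample grows. The article gives no value for d or h.

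**The case against.** The strongest defence is that this is a secondary, exploratory piece of work. It is done only with more patients, is reported separately, and cannot displace the primary intention-to-treat result. All of that stands and limits the weight of the point.

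A reader might infer that the plan counts any shift as confounding and will almost certainly report false confounders. The article does not support this. It says only that the effects will be compared, and a cut-off may be in an analysis plan that is not shown. At 160 patients the calculated frequency is well short of certainty, and 7 of the 18 candidates are not baseline variables, so they do not belong in that count.

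A reader might also infer that a baseline variable can never confound a randomized comparison. That is too strong here. Under unequal allocation by municipality, any baseline variable that differs between A and B is systematically unbalanced in a pooled analysis. The per-protocol comparison sets compliers against controls and is not randomized, so confounding is a proper question there.

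The 0.01 level is a genuine precaution for the interaction tests, but it supplies no criterion for a shift. A missing cut-off is also not the main problem: whatever the cut-off, the comparison does not measure confounding by baseline covariates within municipality.

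**Conclusion.** The point holds for the exploratory intention-to-treat analysis. The comparison cannot identify confounders: within municipality, shifts on baseline covariates are chance, and shifts on later covariates may be mediation or selection. The frequency of spurious findings, 66–88% at 54 patients and 5–32% at 160, rests on an assumed 1-point cut-off, independent covariates and correlations of 0.1 to 0.2. It is lower with a stricter cut-off. Municipality, the one design-based confounder, is absent from the candidate list and from the analysis of variance as described; the bias is d/3 if A and B are of equal size, and less once the third municipality is counted.

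This should be changed, but it does not threaten the trial's main conclusion. The primary model stands and already includes municipality.

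**What to change.** - Remove the confounder comparison from the intention-to-treat analysis.
- Include municipality in the analysis of variance.
- Report one model, specified in advance, adjusted for municipality and a short set of baseline covariates (for example baseline DEMMI, age and OMC), labelled as a precision or sensitivity estimate. The exact set is a judgement; what matters is that it is fixed beforehand. Adjustment for baseline DEMMI is already planned for the main report.
- Keep the baseline variables for the group-by-covariate interaction analyses at the 0.01 level.
- Keep variables measured after randomization out of the adjusted treatment effect.
- Limit any assessment of confounding to the per-protocol comparison, and say there that the comparison is not randomized.

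The cost is a change of wording and somewhat less analysis. What is lost is the table of one-by-one adjusted intention-to-treat estimates. No data collection changes.
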